**Methods:**

A controlled non-randomised two group (intervention vs treatment-as-usual control) design, using an intention-to-treat model, will evaluate the effectiveness of a suicide prevention aftercare intervention providing follow-up after presentations to a hospital emergency department as a result of a suicide attempt or high risk for suicide. The intervention is a community-based service, utilising two meetings with a mental health clinician and follow-up contacts by peer workers via a combination of face-to-face and telephone for four weeks, with the option of extension to 12 weeks. Seventy-five participants of the intervention service will be recruited to the study and compared to 1265 treatment-as-usual controls. The primary hypotheses are that over 12 months, those who participate in the aftercare follow-up intervention are less likely than controls to present to a hospital emergency department for a repeat suicide attempt or because of high risk for suicide, will have fewer re-presentations during this period and will have lower all-cause mortality. As a secondary aim, the impact of the intervention on suicide risk factors for those who participate in the service will be evaluated using pre- and post-intervention repeated measures of depression, anxiety, stress, hopelessness, belongingness, burdensomeness, and psychological distress. Enrolments into the study commenced on 1 November 2017 and are anticipated to cease in November 2019.

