## Methods/design

### Study aims

The primary objectives of the study are to evaluate the impact of the Aftercare intervention on the likelihood of a re-presentation to an emergency department as a result of a suicide attempt or because of high risk for suicide, the rates of re-presentation to emergency departments as a result of one or more repeat suicide attempt(s) or because of high risk for suicide, and the number of deaths by any cause. The secondary objectives of the study are to evaluate the impact of the Aftercare intervention on factors associated with increased risk of suicide, namely, mood [64], hopelessness [65, 66], belongingness, burdensomeness [66], and psychological distress [67, 68].

It is hypothesised that;
Participants of the Aftercare intervention will be less likely to have a repeat presentation to an emergency department within 12 months as a result of a suicide attempt or being at high risk for suicide than non-participants.Participants of the Aftercare intervention will have lower rates of re-presentations to a hospital emergency department for suicide attempt or high risk for suicide within 12 months than non-participants.Participation in the Aftercare intervention will be associated with fewer all-cause deaths within 12 months than non-participation.For participants of the Aftercare intervention, depression, anxiety, stress, hopelessness, belongingness, burdensomeness, and psychological distress will be improved in comparison to baseline levels following the intervention.

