### Data analysis

Analyses will be conducted using the Statistical Package for the Social Sciences version 25 [85] and SAS v9.4 [86]. Primary analyses will be conducted according to the intention-to-treat approach. Presentations to an emergency department with a repeat suicide-related event and for all-cause death will be compared between the two non-randomised groups (intervention vs control) using a Kaplan Meier plot where the initial presentation to an emergency department is designated as time zero, and using censoring. A log-rank test will compare the Kaplan Meier curves of the two groups.

A negative binomial regression model will be applied to the data to estimate the effect of the intervention on re-presentation rates, accounting for varying lengths of follow-up period and adjusting for service and person-level characteristics (e.g. facility, age, sex, indigenous status) and censoring.

To investigate the impact of the service on suicide risk factors (secondary outcome measures), a comparison of pre- and post-intervention outcome measures will be conducted for participants of the intervention using paired t-tests, or a Wilcoxon signed-ranks test (if the sample is non-normally distributed), adjusting for multiple comparisons (Bonferroni correction).

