### Sample size and statistical power

The sample size required to achieve power of 80% was estimated for the primary analyses using G*Power [87]. Local hospital data (2014/2015 year) indicated that approximately 1340 people present to emergency departments with suicide-related presentations annually and systematic reviews have estimated that 16% re-attempt suicide within 12 months [5]. Based on Hvid et al.’s [30] report that an intervention group had approximately half the rate of deaths by suicide than a TAU group at 12 months (.087 vs .219), the sample size required for a log-rank test at α level .05 is 75 participants in the intervention group and 1265 participants in the control group.

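### Holm's step-down procedure would serve the seven pre-post scales better than single-step Bonferroni at the same family-wise bound: a low-priority efficiency gain, not an error

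*Protocol article*

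**What the plan says.** The Data analysis section of the protocol article compares pre- and post-intervention scores within the intervention group "using paired t-tests, or a Wilcoxon signed-ranks test (if the sample is non-normally distributed"), "adjusting for multiple comparisons (Bonferroni correction"). It does not state how many tests form the family, the family-wise level, or any stepwise version of the correction.

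The family can be counted from hypothesis 4 under Study aims: "depression, anxiety, stress, hopelessness, belongingness, burdensomeness, and psychological distress will be improved in comparison to baseline levels". That is seven constructs. They match the instruments under Secondary outcomes: three DASS-21 scales, two INQ scales, the BHS-SF and the K-10.

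The section on sample size and statistical power covers only the primary hypotheses: "The sample size required to achieve power of 80% was estimated for the primary analyses using G*Power". The .05 level appears there for the log-rank test alone.

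**The concern.** Single-step Bonferroni holds every scale to the strictest threshold, however many of the other scales have already shown a clear change. Holm's procedure relaxes the threshold as hypotheses are rejected and keeps the same bound on the family-wise error. For testing, it can therefore only match or add to what Bonferroni rejects.

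At stake is power to say which scales improved. Hypothesis 4 names each construct, so scale-by-scale conclusions are part of the stated question. There are at most 75 pairs, and fewer if some participants do not complete the measures at discharge. The sample was not sized for these tests.

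**Working it through.** **Inputs**

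- Number of tests: 7, counted from hypothesis 4.
- Family-wise level: .05, two-sided. Assumed, because the article states alpha only for the log-rank test.
- Pairs: at most 75, from "Seventy-five participants of the intervention service will be recruited to the study". The number with a post-measure is not given; 50 is an assumed lower case.
- Standardised mean changes and correlation between scales: not in the article. Assumed changes run from 0 to 0.8 SD, with a correlation of .5 unless stated otherwise.

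The article gives no per-test level or power for this analysis, so there is no figure of its own to reproduce.

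**Thresholds**

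- Bonferroni: every p-value against .05/7 = .0071.
- Holm: ordered p-values, smallest first, against .05/7, .05/6, .05/5, .05/4, .05/3, .05/2 and .05/1 = .0071, .0083, .0100, .0125, .0167, .0250 and .0500, stopping at the first failure.

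The first step is the same, so the chance of at least one rejection is the same. Every later Holm threshold is larger, so Holm keeps every Bonferroni rejection.

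**Validity of the planned method.** For seven independent tests with no true change:

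- unadjusted: 1 − (1 − .05)^7 = .302
- Bonferroni: 1 − (1 − .05/7)^7 = .0489

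The planned correction does its job.

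**Power.** Seven correlated paired t-tests were simulated, 20,000 runs per scenario, with 75 pairs and correlation .5 unless noted:

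| True changes (SD) | Power reported for | Bonferroni | Holm |
|---|---|---|---|
| one at 0.3, six null | the one scale | 44% | 44% |
| all seven at 0.8 | average scale | 100% | 100% |
| four at 0.4, three null | average of the four | 76% | 79–80% |
| two at 0.6, one at 0.3, four null | the weak scale | 44% | 49% |
| all seven at 0.35 | average scale | 61% | 72% |
| all seven at 0.4 | average scale | 75% | 86% |
| six at 0.6, one at 0.3 | the weak scale | 44% | 73% |
| six at 0.6, one at 0.3, 50 pairs | the weak scale | 26% | 54% |

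With all seven at 0.4 SD, the chance of showing all seven improvements is 37% under Bonferroni and 69% under Holm. In every simulated data set Holm rejected whatever Bonferroni rejected.

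**Error control.** With all seven null and 75 pairs, the family-wise error is the same for both methods: .047, .042 and .033 at correlations 0, .5 and .7. With some scales null the methods differ, though both stay below .05:

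- four at 0.4 SD, three null: .018 (Bonferroni), .033 (Holm)
- four at 0.6 SD, three null: about .02 (Bonferroni), about .045 (Holm)

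**The case against.** The strongest reply is that nothing is wrong. The article prespecifies a valid, conservative correction for secondary outcomes, and choosing between two valid procedures can look like a reviewer's taste. On that view extra conservatism is defensible for a pre-post comparison with no control group. This stands in part: Bonferroni is not an error, and no other statement in the article contradicts it. It does not remove the point, because at the same family-wise bound Holm dominates Bonferroni for testing and needs no further assumption.

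Three stronger readings are tempting, and the article supports none of them.

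- *That nothing at all is given up.* Holm gains its power by using slack that Bonferroni leaves, so its actual family-wise error moves closer to .05 when some scales are null. Simultaneous confidence intervals that match Holm are also less simple. This second cost is small here, since the Data analysis section mentions only tests for these measures.
- *That the weaker scales lose substantial power.* This depends on unknown inputs. The rise from 44% to 73% needs six scales at 0.6 SD and exactly one at 0.3 SD, which is close to Holm's best case because the weak scale is then tested at nearly .05. Other equally possible inputs give no gain.
- *That Holm makes a positive finding more likely overall.* The chance of at least one significant scale does not change.

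One could also say that an unseen analysis plan may specify a stepwise version. The article names Bonferroni without qualification, so its ordinary single-step meaning is the fair reading.

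**Conclusion.** The point holds as an efficiency improvement of low priority. With 75 pairs and a correlation of .5, the gain in per-scale power ranges from nil to about 29 points. It is about 4 points when four scales improve by 0.4 SD and three do not, and 11 to 12 points when all seven improve by 0.35 SD. The upper end is a favourable case, not an expected one. These figures rest on assumed effects, correlation, family-wise level and number of pairs; the dominance of Holm over Bonferroni at the same bound does not.

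Hypotheses 1 to 3 are untouched, and Holm does nothing about the lack of a control group for hypothesis 4.

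**What to change.** In the Data analysis section, replace the bracketed reference to the Bonferroni correction with: *(Holm step-down procedure across the seven scales, family-wise .05)*. This also states the size of the family and the level, which the sentence now leaves implicit. Make the change before the secondary data are analysed.

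The cost is one phrase. No new data or different tests are needed, since Holm works on the p-values from either the paired t-tests or the Wilcoxon tests. If simultaneous intervals are wanted, they can be reported at the Bonferroni level, with a note that they may be wider than the Holm decisions imply.

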### Sample size and statistical power

The sample size required to achieve power of 80% was estimated for the primary analyses using G*Power [87]. Local hospital data (2014/2015 year) indicated that approximately 1340 people present to emergency departments with suicide-related presentations annually and systematic reviews have estimated that 16% re-attempt suicide within 12 months [5]. Based on Hvid et al.’s [30] report that an intervention group had approximately half the rate of deaths by suicide than a TAU group at 12 months (.087 vs .219), the sample size required for a log-rank test at α level .05 is 75 participants in the intervention group and 1265 participants in the control group.

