The first landmark study evaluating the impact of a coordinated aftercare service was conducted on the outskirts of Oslo, Norway [28]. In what became known as ‘the Bærum Model’, people who presented to hospital after attempting suicide (but were not directly admitted) were followed up with home visits for up to 6 months and provided with support via a combination of face-to-face and phone contacts. There were four components to the support offered: (1) outreach – immediate, assertive outreach and follow-up after discharge from hospital, (2) problem-solving – solution focused counselling, (3) adherence – encouragement to remain engaged with treatment and follow recommendations, and (4) continuity – maintain contact with a consistent group of support people [29]. This intervention was credited with having contributed to a significant reduction in suicidal behaviours, from 170 per 100,000 in 1984 to 79 per 100,000 in 1995; a reduction of 53.5% [28].

These findings were supported by a Danish randomised controlled trial of a 6-month aftercare service based on the Bærum Model [30], in which 69 intervention participants were compared with 64 treatment-as-usual controls. The researchers found that significantly fewer people in the intervention group re-attempted suicide (8.7%) than the control group (21.9%) over a 12-month period. This study also found reduced numbers of repeated acts (8 in the intervention group versus 22 in the control group). The researchers noted that a key characteristic of the intervention was its “swift and rather aggressive outreach” [30] p.296, as well as the capacity to adapt the support to account for personal factors. A 5-year follow-up study found the number of people with repeated suicide attempts remained lower for the intervention group for up to 3–4 years, and the total number of repeat suicide attempts remained lower for the intervention group after 5 years [31].

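### The power paragraph labels re-attempt rates as suicide deaths, calls a 60% reduction about half, and leaves the control rate open; 80% power holds two-sided only for 21.9% vs 8.7%

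*Protocol article*

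**What the plan says.** All of the justification is in the protocol article, section Sample size and statistical power. It sets the target: "The sample size required to achieve power of 80% was estimated for the primary analyses using G*Power". It gives two background figures: "approximately 1340 people present to emergency departments with suicide-related presentations annually", and "systematic reviews have estimated that 16% re-attempt suicide within 12 months". It then draws the effect from a Danish randomised trial, saying the intervention group had "approximately half the rate of deaths by suicide than a TAU group at 12 months (.087 vs .219"), and concludes that "the sample size required for a log-rank test at α level .05 is 75 participants in the intervention group and 1265 participants", the 1265 being controls. The two groups add up to the 1340 annual presenters.

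The Background describes the same Danish trial, under the same reference number, differently: "significantly fewer people in the intervention group re-attempted suicide (8.7%) than the control group (21.9%) over a 12-month period".

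Under Data analysis the planned comparison is: "A log-rank test will compare the Kaplan Meier curves of the two groups". This covers time to a repeat suicide-related presentation and time to death from any cause. Neither section says whether the test is one- or two-sided.

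**The concern.** Three things in the power paragraph do not fit together.

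1. **Endpoint.** The same pair of rates is suicide deaths in one section and re-attempts in another. All-cause death is one of the three primary outcomes, so a reader of the power paragraph alone could believe that the study was sized on mortality.
2. **Effect size.** The words describe a halving; the printed rates describe a 60% reduction. These are different targets, and the smaller effect needs a larger sample.
3. **Control rate.** Two candidate 12-month rates appear, 16% and 21.9%, and the text does not say which one entered the calculation or what the other is for.

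What is at stake is how a null result is read. If readers take the study to have 80% power for a halving, or at a 16% base rate, they will treat a non-significant log-rank test as stronger evidence against the intervention than it is.

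**Working it through.** **Inputs.** n₁ = 75 and n₂ = 1265, so k = 1265/75 = 16.87; α = .05; target power 80%; printed rates p₁ = .087 and p₂ = .219; second quoted base rate .16. All come from the sample size section. Sidedness is not stated, so two-sided is taken as the working case.

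**Effect size.** .087/.219 = 0.397, a 60% reduction. A true halving of .219 would be .1095. The 0.397 ratio applied to 16% gives .16 × 0.397 = .0636 (6.4%), a rate the document does not print.

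**Formula.** With p̄ = (p₁ + k·p₂)/(1 + k), d = p₂ − p₁, A = √[p̄(1 − p̄)(1 + 1/k)] and B = √[p₁(1 − p₁) + p₂(1 − p₂)/k]:

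- n₁ = [(z_α·A + z_β·B)/d]²
- continuity-corrected n₁ = (n₁/4)·{1 + √[1 + 2(1 + 1/k)/(n₁·d)]}²
- power at n₁ = 75, uncorrected = Φ[(d√75 − z_α·A)/B]

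**Reproducing the plan's figure (.087 vs .219, two-sided).** p̄ = .2116, A = .4204, B = .2993, d = .132.

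- Uncorrected: [(1.960 × .4204 + 0.842 × .2993)/.132]² = 66.4, so 67.
- Corrected: 74.2, so **75**, matching the plan. Power at 75 vs 1265 is 80.6% corrected and 85.7% uncorrected.
- Simulated two-sided log-rank test (exponential times, censoring at 12 months): about 84%.

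The stated size is therefore reproducible two-sided from the printed rates, although by a two-proportion formula. The usual event-based log-rank formula (Schoenfeld) gives 97% on these rates. That is over-optimistic at about 1:17 allocation, where the intervention arm expects only 75 × .087 = 6.5 events.

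**A second route to 75.** .0636 vs .16, one-sided, uncorrected, gives n₁ = 74.2, so 75 (80.5% power). The document cannot tell us which route was taken.

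**Two-sided power of 75 vs 1265 under each reading:**

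| Control vs intervention | Reading | Two-proportion z, uncorrected | Simulated log-rank |
|---|---|---|---|
| 21.9% vs 8.7% | rates as printed | 86% | 84% |
| 16% vs 6.4% | printed ratio at the 16% rate | 66% | 65–66% |
| 21.9% vs 10.95% | halving of 21.9% | 65% | 63–64% |
| 16% vs 8% | halving of 16% | 45% | 45% |

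Worked example for the last row: A = .3730, B = .2856, d = .08, so (.08 × 8.660 − 1.960 × .3730)/.2856 = −0.134 and Φ(−0.134) = 44.7%.

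**The case against.** The strongest reply is that the sample size is sound. The sentence bases itself on .087 vs .219 and then gives 75 and 1265, and a standard two-sided calculation on exactly those rates returns 75. It needs no figure that is not printed and no undeclared one-sided test. On that reading the 16% is context beside the annual number of presenters, the reference to half is loose wording next to exact figures, and unstated sidedness in a condensed article is at most a point to clarify. In addition, the trial's endpoint is emergency department re-presentation for an attempt or for high suicide risk, which is broader than re-attempt, so 16% is not established as its control rate.

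Most of this stands. A reader who finds the one-sided 16% vs 6.4% route might infer that the 80% depends on a hidden one-sided test and that the true two-sided power is 66%. The document does not support that: the printed rates give 75 two-sided, and the 66% rests on a 6.4% rate built by the reader. The 66%, 64–65% and 45% are sensitivity figures, not corrections to the calculation.

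The reply does not remove the contradiction over what the rates measure, nor the mismatch between halving and 0.40. The breadth of the endpoint also cuts both ways: it leaves 21.9%, taken from a 64-person control arm, no better established than 16%.

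**Conclusion.** The power justification misdescribes its own inputs. The endpoint label contradicts the Background, and the verbal effect size contradicts the printed rates; both are visible without any reconstruction. The role of the 16% rate and the sidedness are left open.

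The sample size is not shown to be wrong. At 75 vs 1265, 80% two-sided power is supported for a fall from 21.9% to 8.7% (80.6% corrected, about 84% by simulated log-rank) and, among the readings the paragraph invites, for that one only. Two-sided power is about 66% if the same ratio applies at a 16% control rate, about 64–65% for a halving of 21.9%, and about 45% for a halving of 16%. Nothing in the paragraph supports an 80% claim for all-cause death.

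The figures assume two-sided α .05, no loss to follow-up before 12 months and, for the simulations, exponential event times. They treat re-attempt rates as a stand-in for the broader re-presentation endpoint, whose control rate the document does not give.

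**What to change.** Keep the sample and rewrite the one paragraph:

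- Describe .087 vs .219 as 12-month re-attempt rates, in line with the Background.
- Replace the description as about half with the actual ratio, about 0.40 (a 60% reduction).
- State the control rate, sidedness and formula that the sponsor actually used, and what the 16% contributes. The sponsor should supply these from its own calculation; 16% vs 6.4% should not be written in as if it were the design assumption.
- Say that the 80% applies to 21.9% vs 8.7%, and not to a halving, a 16% base rate or all-cause death.
- Report two-sided power for the alternatives: about 66% (16% vs 6.4%), about 64–65% (halving of 21.9%) and about 45% (halving of 16%).

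No extra participants and no change to the analysis are needed. The downside is that the stated power looks less favourable, and a null result will have to be reported with that limit in view.

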## Discussion

This study aims to contribute to our understanding of effective interventions for people at high-risk for suicide, with the intention of quantifying any impact on the number of presentations to emergency departments for suicide-related events, and all-cause mortality, following an aftercare intervention. The study will provide a real-world examination of an innovative aftercare follow-up service for people who have presented to a hospital emergency department following a suicide attempt or because of high risk for suicide. Specifically, the study will expand upon our understanding of follow up in suicide prevention [35, 88], extend literature regarding peer worker integration in treatment models of suicidal persons, and inform future policy decisions.

### Limitations

The study groups are non-randomised, hence intervention participants are self-selecting and may therefore constitute a group that is inherently different from controls prior to study commencement, such as having higher motivation to seek treatment or greater levels of psychological mindedness. Controlling such factors will require future randomised controlled trials. The current study is typical of pragmatic trials which test the effectiveness of interventions in a real-world context as opposed to efficacy trials which are in controlled conditions.

